### Participant timeline

The participant timeline of this study is shown in Fig. 1.

**Fig. 1 Fig1:**
[figure not shown]
Participant flowchart. HBV, hepatitis B virus; HCC, hepatocellular carcinoma

### Sample size

We estimated using PASS 15.0.5 that we would need at least 108 subjects in each group, assuming 3-year rates of recurrence-free survival of 64% among those on entecavir monotherapy [23] and anticipated 79% among those on TDF monotherapy, enrollment lasting two years and follow-up lasting five years. This sample should be able to detect a significant difference between the groups with 90% power and bilateral α = 0.05. We increased the total number from 216 to 240 to compensate for 10% loss to follow-up.

### Assignment of interventions: allocation

#### Sequence generation

Statisticians will generate randomization cards using stratified randomization according to sex, tumor stage, and preoperative titer of HBV DNA.

#### Concealment mechanism

Allocation information will be kept in sealed envelopes. The envelopes and internal original records will be kept by the department for future reference.

#### Implementation

After participant eligibility has been confirmed, a specially designated person will open the sealed envelope to obtain the random number, which will serve to assign patients 1:1 to either group.

### Assignment of interventions: blinding

#### Who will be blinded

Study investigators and participants, but not data analysts, will be aware of group allocation.

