### Trial design

This study is a phase 3 randomized, open-label, superiority trial. Participants will be randomly divided into two groups in a ratio of 1:1, one of which will receive TDF monotherapy and the other will receive entecavir monotherapy during the peri- and postoperative period. The primary outcome of the study is the rate of recurrence-free survival at 1, 3 and 5 years after curative hepatectomy. The secondary outcomes are the rate of overall survival at 1, 3, and 5 years; adverse reactions; virological response; rate of alanine transaminase normalization; and seroreactivity at 24 and 48 weeks after surgery.

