### Outcomes

Patients will receive routine follow-up every month for the first three months, every two months for six months to two years, then every six months thereafter. At each follow-up, tests will be performed to assess liver function, HBV DNA load, virological response, serum alpha fetoprotein level, and other hematological indicators. Each follow-up will also involve liver ultrasonography as well as contrast-enhanced computer tomography of the chest and abdomen or magnetic resonance imaging of the abdomen (Table 1).

**Table 1 Tab1:** Study assessment measures

Assessment measures	Preoperation	Postoperative day 5	One month after surgery	Two months after surgery	Three months after surgery	Six months after surgery	Every six months until HCC recurrence /metastasis or death
Blood routine examination	x	x	x	x	x	x	x
Urine routines	x	x	x	x	x	x	x
Stool routine examination	x	x	x	x	x	x	x
Liver function	x	x	x	x	x	x	x
Renal function	x	x	x	x	x	x	x
Myocardial enzyme	x	x	x	x	x	x	x
Hepatitis B virological test^1^	x		x	x	x	x	x
Coagulation function	x	x	x	x	x	x	x
Lipid level^2^	x		x	x	x	x	x
Alpha fetoprotein	x		x	x	x	x	x
Des-gamma-carboxy prothrombin	x		x	x	x	x	x
Hepatits C antibody	x						
Human immunodeficiency virus antibody	x						
• Blood HCG test^3^	x						
Electrocardiogram	x		x	x	x	x	x
Abdominal ultrasonography	x		x	x	x	x	x
Chest and upper abdomen enhanced MRI/CT	x		x	x	x	x	x

*CT* Computed tomography, *HCC* Hepatocellular carcinoma, *MRI* Magnetic resonance imaging, *RFS* Recurrence-free survival, *OS* Overall survival

1. Including hepatits B surface antigen, hepatits B surface antibody, hepatits B e antigen, hepatits B e antibody, hepatits B c antibody, and hepatits B virus DNA

2. Including triglyceride, cholesterol, high-density lipoprotein, and low-density lipoprotein

3. Women of childbearing age

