The primary outcome is recurrence-free survival, defined as the time between the randomization date and first occurrence of HCC recurrence, as detected by imaging. Recurrence can be extrahepatic or new intrahepatic. The secondary outcomes of this trial include overall survival, defined as the time between the randomization date and death. If the participant is alive at the end of the study or is lost to follow-up, the last follow-up visit will be used. Other secondary outcomes are virological response, defined as titer of HBV DNA; rate of alanine transaminase normalization; seroreactivity at 24 and 48 weeks after resection, defined as the presence of HBsAg or HBV e antigen; frequency of treatment-related adverse events, as assessed using the Common Terminology Criteria for Adverse Events (version 5.0) [32]; and treatment tolerability, measured in terms of the proportion of patients completing the planned treatment.

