### Data collection and management

#### Plans for assessment and collection of outcomes

Assessment measures and corresponding timing are listed in Table 1. Research staff conducting the pre- and post-treatment, and follow-up assessments will receive specific training. Study instruments used for the assessments will be maintained daily according to the requirements of the corresponding department.

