### Statistical methods

#### Statistical methods for primary and secondary outcomes

All statistical analyses will be conducted in a blinded manner. Data will be reported as mean ± SD, and inter-group differences in continuous variables will be assessed for significance using Student's *t* test, while differences in categorical variables will be assessed using the chi-squared test. Survival curves will be calculated using the Kaplan–Meier method and compared using the log-rank test. Cox regression will be applied to identify factors associated with primary and secondary outcomes.

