## Discussion

Entecavir and TDF are both standard first-line treatments for patients with chronic hepatitis B. However, the long-term efficacy of monotherapy with entecavir or TDF in preventing tumor recurrence for patients with HBV-related HCC after curative hepatectomy are still controversial and need to be further verified.

This study will analyze numerous outcomes related to prognosis, including adverse events, virological response, rate of alanine transaminase normalization, and seroreactivity. The results of this study will help to advance our understanding of the long-term efficacy of entecavir or TDF monotherapy. A randomized controlled trial with small sample size comparing the efficacy of TDF (*n* = 74) and entecavir (*n* = 74) monotherapy for patients with HBV-related HCC after curative treatment found TDF therapy was associated with a significantly lower risk of tumor recurrence than entecavir therapy [33]. Our randomized trial with large sample size will provide more stronger evidence about the efficacy of entecavir or TDF monotherapy for patients with HBV-related HCC after curative resection. In general, the larger the sample size and the longer the follow-up, the more reliable the results. We had planned to revise the reference [27] for the sample size calculation, expecting to enroll 638 cases, but did not get approval from the Ethics Committee of Guangxi Medical University Cancer Hospital. The Ethics Committee is of the view that since this study is not directly supported by sufficient funding, there is a risk that if the sample size is further expanded, it may not be successfully completed in accordance with the intended objectives.

A limitation worth noting is that participants will know their assigned treatment may lead some to request conversion of their treatment, triggering their exit from the study.

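### No blinded assessment of the primary event is provided for: only the data analysts are named as unaware of allocation, and blinding the analysis cannot correct a differential call or date of recurrence

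*Protocol article*

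**What the plan says.** The Trial design section declares: "This study is a phase 3 randomized, open-label, superiority trial". The section on who will be blinded is one sentence: "Study investigators and participants, but not data analysts, will be aware of group allocation". The Statistical methods section adds "All statistical analyses will be conducted in a blinded manner", which concerns the analysis only.

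The Outcomes section gives the primary outcome as recurrence-free survival, "defined as the time between the randomization date and first occurrence of HCC recurrence, as detected by imaging". It does not name death as an event in that definition, so as written every primary event depends on the interpretation of an image and on the date given to it.

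On assessment, the article says "Research staff conducting the pre- and post-treatment, and follow-up assessments will receive specific training". It mentions no masking of those staff, no central reading and no endpoint committee. Under Data management, study investigators complete the case report forms. A clinical research assistant reviews them, the investigators sign, and the entries can then no longer be changed. The data monitoring section describes checks for consistency and missing data, not adjudication of recurrence.

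The only open-label limitation that the Discussion admits is that "participants will know their assigned treatment may lead some to request conversion of their treatment, triggering their exit from the study". Outcome assessment is not mentioned there.

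**The concern.** Someone has to decide that a lesion on CT or MRI is recurrent carcinoma, and on which date. A small or equivocal nodule can be called at once or watched until the next scan. If that decision is influenced by knowledge of the drug, the arms differ in recorded events or dates without differing in disease.

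Blinded analysts cannot detect or undo this. They receive events and dates that were recorded and locked before they began. The article therefore places its one safeguard after the point at which bias would enter.

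At stake is the credibility of the primary comparison. A significant difference in recurrence-free survival would face the objection that the event was not assessed blind, although masked reading is compatible with open-label treatment and costs little.

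**Working it through.** **1. The plan's own figure.** The Sample size section gives 3-year rates of 64% (entecavir) and 79% (TDF), 90% power, two-sided α = 0.05, two years of enrolment and five years of follow-up.

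- Hazard ratio = ln(0.79)/ln(0.64) = 0.528.
- Events (Schoenfeld) = 4(1.960 + 1.282)²/(ln 0.528)² = 103.1, taken as 104.
- With exponential survival, uniform 2-year enrolment and 5 further years, the mean event probability is 0.482. Then 104/(2 × 0.482) = 107.9, that is 108 per arm.
- 216/0.90 = 240.

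The stated size reproduces. It supports reading the timeline as 2 + 5 years, which is used below. The point does not depend on the sample size and does not change it.

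**2. A trial with no true difference.** Both arms at 64%, 120 per arm.

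- Hazard λ = −ln(0.64)/3 = 0.1488 per year.
- Event probability = 1 − [exp(−5λ) − exp(−7λ)]/(2λ) = 0.589.
- Events per arm = 120 × 0.589 = 70.7, or 141.3 in all.

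**3. Late calls in one arm.** This is the mechanism that a watched nodule suggests. The assumed delay is six months, the longest visit interval in the Outcomes text ("every two months for six months to two years, then every six months thereafter"). Trials were simulated under step 2. A fraction of TDF recurrences was recorded six months late, and a log-rank test was run on each trial (20,000 trials per row). The last column includes separate repeat runs.

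| TDF recurrences called late | Mean shift in z | Two-sided error |
|---|---|---|
| none | 0 | about 5% |
| 20% | 0.15 | about 5% (5.2% to 5.4%) |
| 50% | 0.38 | about 6.6% (6.6% to 6.7%) |
| 100% | 0.76 | about 12% (11% to 12%) |

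Six months is the less favourable assumption. The Outcomes text has visits every two months in the middle period, whereas Table 1 has six-monthly assessments after month 6. The two must be reconciled. Where visits are closer together, a one-visit delay is shorter and its effect smaller.

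**4. Events recorded differently, not merely late.** Suppose instead that the recorded TDF hazard is lower throughout by a constant factor HR, although the true hazards are equal.

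- Total events d = 120 × [event probability at λ + event probability at HR × λ].
- Shift in z: s = √(d/4) × |ln HR|.
- Two-sided error = Φ(−1.96 + s) + Φ(−1.96 − s).

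| Spurious HR | d | s | Two-sided error | Apparent 3-year rate on TDF (0.64^HR) |
|---|---|---|---|---|
| 0.90 | 136.8 | 0.62 | about 9.4% | 66.9% |
| 0.85 | 134.3 | 0.94 | about 15.6% | 68.4% |
| 0.80 | 131.8 | 1.28 | about 25% | 70.0% |

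Against 141.3 events, these rows mean a net 4.5, 7.0 and 9.5 fewer recurrences recorded on TDF. A six-month delay does not reach the last two rows even when every TDF recurrence is affected. They need recurrences that are never recorded in one arm, or false calls in the other.

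The fractions, the delay and the spurious hazard ratios in steps 3 and 4 are assumptions. The article gives no figure for any of them.

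**The case against.** The strongest reply is that the article never says who reads the scans. The blinding sentence covers investigators, participants and analysts, and does not mention hospital radiologists. Investigators who complete and sign a form may only be transcribing a radiology report, written perhaps by someone who never saw the allocation. A reader might infer that recurrence is judged by people who know the drug. The documents do not establish that. What stands is narrower: the section that exists to say who is blinded names only the analysts, and no other section adds a masked assessor.

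A reader might also infer that the bias would favour TDF, because the planned rates are 79% against 64% and some cited studies point that way. The planned rates are a sample-size input. The Introduction reports divergent evidence, and the explanation of comparators calls long-term efficacy controversial. Nothing shows how readers lean. Nor may the 16% and 25% error rates be attached to watching a nodule until the next visit, as step 4 shows. At modest fractions of late calls the effect can hardly be told from none.

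Imaging follows the same schedule in both arms, which limits differential timing of scans. It does not govern how they are read. Open-label treatment is declared, but it does not require open assessment. A fuller protocol might name a masked reader. However, the article answers the question of blinding explicitly, so this is not a detail that it merely leaves out.

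**Conclusion.** The point holds as a gap in protection, not as a demonstrated bias. As written, the trial provides for no blinded assessment of a primary event that rests on image interpretation, and blinding the statistics cannot remove a differential call or date.

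The size is unknown. If the only effect were a six-month delay in calling TDF recurrences, the two-sided error would stay near 5% when a fifth were delayed, and reach about 6.6% at half and about 12% at all. Rates of about 9% to 25% belong to a spurious hazard ratio of 0.90 to 0.80, which requires differential recording of events. All these figures assume no true difference, exponential survival at 64% at 3 years, 120 per arm and 2 + 5 years. They are illustrations, not estimates.

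The change should be made because it costs little and removes an avoidable objection to the primary result.

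**What to change.** In the section on who will be blinded, and in the section on plans for assessment and collection of outcomes, state that:

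- the radiologist who routinely reports each follow-up CT or MRI is not told the allocation, and the drug name is left off the imaging request;
- the recurrence call and date on the case report form are taken from that report, with the scan date as the event date;
- where the investigator's opinion differs, it is recorded separately and used in a sensitivity analysis.

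The cost is protocol wording and a change to the imaging request. Treatment stays open-label, the sample size stays at 240, and no extra reader or scan is needed, which matters because the Discussion reports limited funding. Recruitment was still open at version 1.1, so later readings can be covered. The date of the change should be noted so that earlier readings can be identified. One small downside remains: masking is imperfect where the hospital record shows the drug.

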#### Procedure for unblinding if needed

Under special circumstances, the data on informed consent forms, allocation information, and paper-based case report forms (CRFs) may be shared with appropriate personnel in the event of a medical emergency or audit by regulatory agencies.

### Data collection and management

#### Plans for assessment and collection of outcomes

Assessment measures and corresponding timing are listed in Table 1. Research staff conducting the pre- and post-treatment, and follow-up assessments will receive specific training. Study instruments used for the assessments will be maintained daily according to the requirements of the corresponding department.

#### Plans to promote participant retention and complete follow-up

This study will not generate extra examination and treatment costs for the participants. Before participants are enrolled, investigators will explain the procedures, benefits, and risks of the trial as well as the participants’ rights, including the right to withdraw from the trial at any time for any reason. Individuals will be enrolled in the study only after signing written informed consent.

#### Data management

Study investigators will complete CRFs for all participants. The CRFs will be reviewed by a clinical research assistant, after which the investigators will sign the forms and the data can no longer be modified. Two investigators will separately enter all participant data into a central database to ensure data accuracy. Once the data have been checked, they will be locked as unmodifiable in the database. Data analysts will then perform all statistical analyses, and the results will be given to investigators, who will write the complete trial report.

The central database will be protected from unauthorized access. Completed CRFs, signed informed consent forms, randomization envelopes, as well as the study protocol and eventual amendments will be archived in a secure location at the study sites for at least five years after completion of the trial.

#### Confidentiality

Informed consent forms, allocation numbers, and CRFs will be stored in a secure location to which only authorized personal have access.

### Plans for collection, laboratory evaluation, and storage of biological specimens for genetic or molecular analysis in this trial/future use

This study will not collect biological specimens for genetic or molecular analyses.

### Statistical methods

#### Statistical methods for primary and secondary outcomes

All statistical analyses will be conducted in a blinded manner. Data will be reported as mean ± SD, and inter-group differences in continuous variables will be assessed for significance using Student's *t* test, while differences in categorical variables will be assessed using the chi-squared test. Survival curves will be calculated using the Kaplan–Meier method and compared using the log-rank test. Cox regression will be applied to identify factors associated with primary and secondary outcomes.

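### HBV DNA titre is compared by an unadjusted t test although the preoperative titre is measured and used to stratify; adjusting for it on the log scale would gain precision at almost no cost

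*Protocol article*

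**What the plan says.** All references are to the protocol article.

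- **Outcome.** The Outcomes section lists "virological response, defined as titer of HBV DNA" among the secondary outcomes. As written, this is a continuous quantity.
- **Test.** The section on statistical methods for primary and secondary outcomes states "Data will be reported as mean ± SD" and that "inter-group differences in continuous variables will be assessed for significance using" Student's t test. It names no baseline covariate and no stratum.
- **Baseline value.** Table 1 marks the hepatitis B virological test before the operation, and its first footnote covers "hepatits B c antibody, and hepatits B virus DNA".
- **Randomisation.** Sequence generation specifies "stratified randomization according to sex, tumor stage, and preoperative titer of HBV DNA".
- **Other uses of the baseline titre.** It appears again only as a subgroup factor. The one regression model named is in the sentence "Cox regression will be applied to identify factors associated with primary and secondary outcomes". That is a search for prognostic factors in time-to-event data and does not adjust a comparison of mean titres.

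**The concern.** When a follow-up measurement has a baseline value of the same quantity, a two-sample t test on follow-up alone treats the part predictable from baseline as noise. Here the baseline spread may be wide. Eligibility accepts patients positive for HBsAg, HBV DNA or both, and excludes those already on anti-HBV therapy, so entry titres can run from undetectable to high untreated levels.

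There is also a mismatch between design and analysis. Stratifying on a predictor of the outcome removes part of the chance variation between arms. A t test that ignores the stratification does not credit that removal.

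What is at stake is the chance of seeing a real virological difference between the drugs. The Background gives inhibition of viral replication as the reason for expecting fewer recurrences, so a missed difference would make the recurrence result harder to interpret.

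**Working it through.** **1. The plan's own figure.** The only sample size stated is for recurrence-free survival. It reproduces:

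- Hazard ratio = ln(0.79)/ln(0.64) = 0.528.
- Events (Schoenfeld, 90% power, two-sided 0.05) = 4 × (1.960 + 1.282)² / (ln 0.528)² = 103.1, rounded up to 104.
- With exponential survival, two years of uniform accrual and five further years of follow-up, event probabilities are 0.589 and 0.375. Then 104/(0.589 + 0.375) = 107.9, so 108 per arm.
- 216/0.9 = 240.

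The article gives no SD, effect size or power for HBV DNA. I use 108 per arm as the evaluable number.

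**2. Power with and without baseline adjustment.** Let ρ be the correlation between baseline and follow-up on the analysis scale. It is an assumption, shown as a range. The effect that the t test detects with nominal 80% power is (1.960 + 0.842) × √(2/108) = 0.381 SD. Adjustment multiplies the residual SD by √(1 − ρ²), so

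adjusted power = Φ(2.802/√(1 − ρ²) − 1.960).

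| ρ | SE of t test / adjusted SE | Adjusted power | Patients per arm for the t test's 80% |
|---|---|---|---|
| 0.1 | 1.005 | 80.4% | 107 |
| 0.2 | 1.02 | 81.6% | 104 |
| 0.3 | 1.05 | 83.6% | 98 |
| 0.5 | 1.15 | 89.9% | 81 |

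The last column is 108 × (1 − ρ²).

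**3. Effect of the stratification.** This needs two further assumptions, because the article gives neither an HBV DNA cut-point nor a blocking scheme: a median split of baseline, and allocation balanced within each half. In 3,000 simulated trials of 216 normally distributed patients, the t test reported a mean standard error of 0.136 SD throughout.

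| ρ | True SD of the estimate | Reported SE too large by | Type I error of t test | Power at 0.38 SD: t test / adjusted |
|---|---|---|---|---|
| 0.3 | 0.133 | about 2% | 4.3% | 80% / 83% |
| 0.5 | 0.124 | about 10% | 3.1% | 82% / 89% |
| 0.7 | 0.114 | about 19% | 1.7% | 84% / 97% |

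A run of 20,000 trials gave type I errors of 4.6%, 3.2% and 1.9%. With simple allocation and no balancing, the t test's type I error is about 5% (4.9% at ρ = 0.5).

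**4. Dependence on the scale.** The article states no log transformation. For log-normal titres with log10 SD σ, put s² = (σ ln 10)². The raw-scale correlation is then (exp(ρs²) − 1)/(exp(s²) − 1). At ρ = 0.5 this is 0.07 for σ = 1 and about 0.00002 for σ = 2 (assumed values of σ). On the raw scale, adjustment would gain essentially nothing.

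**5. Dependence on the detection limit.** Take a latent correlation of 0.5 and put a floor under follow-up values. With 80% at the floor, the correlation falls to 0.33 and nominal adjusted power is 84%. With 90% at the floor it falls to 0.26 and power is 83%.

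**The case against.** The strongest reply is that an unadjusted t test is a valid analysis of a randomised comparison. It is unbiased and does not inflate type I error, and no power is claimed for this outcome. That stands: the point is one of efficiency.

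It can also be said that the correlation is unknown and may be low. Everyone is on antiviral treatment, many titres may become undetectable, and the discontinuation criteria change treatment when the titre has not fallen by 3 months after surgery, which can weaken the link to baseline. This also stands, and it is why the gain is given as a range that starts near zero. The detection-limit check shows the gain shrinking but not disappearing.

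Third, the t-test sentence is a general rule and does not name virological response. True, but it stands under the heading for primary and secondary outcomes, and the titre is a continuous secondary outcome. The article states this choice and does not leave it open.

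A reader might infer more than the document supports:

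- **That the t test's confidence interval is wrong because it is too wide.** This requires effective balance within HBV DNA strata at a relevant cut-point, and the article describes neither. Without that balance the test keeps its nominal size.
- **That ALT normalization has the same fault.** The question there is who belongs in the denominator. The article does not say, and a condensed article may leave it to the analysis plan.
- **That virological response is a leading secondary outcome.** The article does not rank its secondary outcomes and lists overall survival first.

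**Conclusion.** The point holds as a low-cost improvement. The stated analysis of HBV DNA titre is valid but gives up precision that the preoperative titre could supply. It is somewhat conservative if the stratification achieves balance.

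On the log scale at 108 per arm, 80% power would become about 80% to 82% at a correlation of 0.1 to 0.2, 84% at 0.3 and 90% at 0.5. These figures assume roughly normal log titres and a linear relation to baseline. The gain is smaller if most titres are below the detection limit, and close to nil if titres are analysed untransformed. Where stratification does balance HBV DNA, the t test already benefits slightly, so the fair comparison at 0.5 is 82% against 89%.

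Only a secondary outcome is affected. The primary analysis and the sample size of 240 do not change.

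**What to change.** In the section on statistical methods for primary and secondary outcomes, replace the t test for HBV DNA with analysis of covariance of log10 HBV DNA at the planned times after surgery. Use log10 preoperative HBV DNA as covariate and include the stratification factors. Use 24 and 48 weeks if those times are meant for virological response; the wording of the outcome lists can also be read as attaching them to seroreactivity only, so state which applies. Give a rule for values below the detection limit, since they have no usable logarithm as they stand. If the proportion with undetectable HBV DNA is reported, compare it by logistic regression with the same covariate.

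The cost is a change of wording, using data already scheduled for collection. The downside is the assumption that follow-up log titre is linear in baseline log titre. The change should be fixed before outcome data are examined by arm.

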### Eligibility criteria

To be enrolled in the study, participants must be 18–75 years old, they must have tested positive for HBsAg and/or HBV DNA at admission, they must have undergone curative hepatectomy at one of the study sites, and their diagnosis of HCC must have been confirmed by postoperative histopathology. Curative resection is defined based on intra- and postoperative criteria [28]. Participants must also have scored 0 or 1 on the ECOG Performance Status Scale at admission. They must be aware of their condition and able to provide written consent.

Potential participants will not be enrolled if they tested positive at admission for antibodies against hepatitis C virus or human immunodeficiency virus, or if they were receiving any anti-HBV therapy before enrollment, such as interferon, entecavir, TDF, adefovir dioxide, or lamivudine. They will also be excluded if they have a history of other malignancies or serious diseases within the previous five years, a history of organ transplantation or drug allergy, autoimmune disease or history of long-term use of glucocorticoids. Pregnant or lactating women will not be considered for enrollment. Participants who fail to comply with treatment or complete follow-up will be excluded from the study.

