#### Methods in analysis to handle protocol non-adherence and any statistical methods to handle missing data

Data analysis of this study will according to the intention-to-treat principle. Efforts are made to follow-up participants who dropped out from treatment in order to obtain more evaluation indexes and recorded in the CRFs. The last assessment data will be applied for patients who lost to follow-up.

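### Seroreactivity is compared by an unadjusted chi-squared test that ignores preoperative antigen status, so never-positive patients are pooled with those who cleared the antigen and power can be substantially reduced

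*Protocol article*

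**What the plan says.** All references are to the protocol article.

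- **Endpoint** (Outcomes): "seroreactivity at 24 and 48 weeks after resection, defined as the presence of HBsAg or HBV e antigen". This is a status at a visit. It does not refer to the preoperative result, to loss or to seroconversion.
- **Test** (Statistical methods for primary and secondary outcomes): "differences in categorical variables will be assessed using the chi-squared test". The only model named in that section is for another purpose: "Cox regression will be applied to identify factors associated with primary and secondary outcomes".
- **Population** (section on non-adherence and missing data): "Data analysis of this study will according to the intention-to-treat principle".
- **Entry** (Eligibility criteria): "they must have tested positive for HBsAg and/or HBV DNA at admission". A patient can enter on HBV DNA alone, and HBeAg is not mentioned.
- **Baseline data** (Outcomes, Table 1, footnote 1): the hepatitis B panel is marked preoperatively and is described as "Including hepatits B surface antigen, hepatits B surface antibody, hepatits B e antigen" and further markers.
- **Randomisation** (Sequence generation): "stratified randomization according to sex, tumor stage, and preoperative titer of HBV DNA". Antigen status is not a stratification factor.

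**The concern.** Antigen status at 24 or 48 weeks depends heavily on status before surgery. A patient who never carried the antigen is non-reactive at both visits whichever drug is given. The stated comparison puts that patient in the same cell as one who carried the antigen and cleared it.

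This has two consequences. First, patients who cannot show a drug effect add variance and dilute the difference between arms, so a real difference in clearance is easier to miss. Randomisation does not balance antigen status by design, so chance differences at entry pass straight into the result. Second, the proportion non-reactive at 48 weeks cannot be read as the proportion who responded serologically. The measurement that would remove both problems is already in the assessment schedule.

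**Working it through.** **The plan's own figure.** No rate or power is given for seroreactivity. The sample size concerns recurrence-free survival only. It reproduces: the hazard ratio is ln(0.79)/ln(0.64) = 0.528, which needs 104 events for 90% power. With two years' accrual and five further years of follow-up, the mean event probability is 0.482, so 104/0.482 = 216 in total, or 108 per arm. Then 216/0.9 = 240, or 120 per arm. I use 120 per arm below.

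**Assumed inputs** (not in the protocol): the share q positive at entry, and the loss by the visit in each arm, a and b. Patients negative at entry are taken to stay negative.

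**Formulas.**
- Plain chi-squared on presence: the proportions are q(1−a) and q(1−b), with mean p. SE = √[2p(1−p)/120], and z is the difference divided by SE.
- Stratified by entry status: the entry-negative stratum contributes nothing. Among 120q patients per arm, the difference is b−a. With l = (a+b)/2, SE = √[2l(1−l)/(120q)].
- Power ≈ Φ(z−1.96), plus the small opposite tail.

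**HBeAg as its own outcome, q = 25%, loss 10% versus 30%.**
- Plain: 22.5% versus 17.5%, difference 0.05, p = 0.20, SE = √(0.32/120) = 0.0516, z = 0.97, power 16%.
- Stratified: 30 patients per arm, difference 0.20, SE = √(0.32/30) = 0.1033, z = 1.94, power 49%.

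The simulated column uses the Mantel-Haenszel test for the stratified result.

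| HBeAg-positive at entry | Formula: plain / stratified | Simulated: plain / stratified |
|---|---|---|
| 15% | 11% / 32% | 11% / 31% |
| 25% | 16% / 49% | 16% / 49% |
| 35% | 23% / 63% | 22% / 64% |

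The gap narrows when clearance is higher or more patients are positive at entry. With 50% positive and loss of 20% versus 50%, simulated power is 70% against 94%.

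**Composite as written (HBsAg or HBeAg), loss 2% versus 10%.** Only patients negative for both antigens at entry are never positive. With 10% double-negative, the plain comparison is 88.2% versus 81.0%: difference 0.072, p = 0.846, SE 0.0466, z = 1.55, power 34%. Stratified, there are 108 per arm: difference 0.08, SE 0.0323, z = 2.48, power 70% by formula and 74% simulated. The formula is rougher here because losses are few.

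| Double-negative at entry | Simulated: plain / stratified | Relative cut |
|---|---|---|
| 10% | 34% / 74% | about 53% |
| 5% | 49% / 76% | about 36% |
| 1% | 71% / 78% | about 8% |
| 0% | 78% / 78% | none |

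If loss is 0.5% versus 2%, power is at most about 12% under either test. The expected losses are then only about 0.6 and 2.4 per 120 patients.

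**Interpretation.** Let a share k be non-reactive at entry and a share l of the rest lose the antigen. The non-reactive proportion at the visit is 1−(1−k)(1−l). With k = 2% and l = 2% this is 1−0.98×0.98 = 3.96%, and 2/3.96 = 51% of those patients were already non-reactive at entry. With k = 10% and l = 0.5% it is 10.45%, and 10/10.45 = 96% were.

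**Validity.** With equal loss in both arms, the plain test rejects in about 5% of simulated trials.

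**The case against.** The strongest objection is that the written outcome is a composite. A patient negative for HBeAg but positive for HBsAg is reactive on it, so the large losses computed for HBeAg alone do not describe it. On the composite, the never-positive group is limited to patients admitted on HBV DNA alone who are also HBeAg-negative. The protocol does not say how many there will be, and there may be few. This stands, and a reader who infers that most power is lost goes further than the protocol supports. That inference needs a separate HBeAg analysis with a minority to half positive at entry, or a composite with about 10% double-negative.

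It is also fair that stratification cannot rescue a composite dominated by persistent HBsAg, that the unadjusted test is valid under randomisation, and that the trial is not sized on this secondary outcome. The protocol calls the outcome seroreactivity and does not label non-reactive patients as responders, so the risk there is misreading, not a false statement.

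A further objection is that denominators and baseline adjustment belong in the analysis plan, which is not shown. This carries less weight. The article does name the endpoint and a test for categorical variables, and an analysis plan that follows both as written would carry the weakness over.

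**Conclusion.** The point holds as a matter of efficiency and interpretation. The stated analysis ignores a strongly prognostic baseline measurement that the trial already collects, and it pools never-positive patients with those who cleared the antigen.

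The size rests entirely on assumed rates at 120 per arm. For HBeAg alone, with 15% to 35% positive at entry and loss of 10% versus 30%, power is about 11% to 22% against 31% to 64%. On the composite with loss of 2% versus 10%, the relative cut runs from none to about half as the double-negative share goes from 0% to 10%. With rare HBsAg loss, both analyses have little power.

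A reader might also infer bias or an inflated false-positive rate. Neither follows, because randomisation protects the unadjusted comparison. The change is worth making because it costs almost nothing, but the primary analysis does not depend on it.

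**What to change.** In Outcomes and in the statistical methods, state that HBsAg and HBeAg are analysed separately at 24 and at 48 weeks. Each analysis is a Mantel-Haenszel (CMH) comparison of the arms, stratified by the preoperative status of the same antigen, with all randomised patients kept in their allocated arm. Alongside it, report loss of each antigen with a risk difference and 95% CI, using patients positive for that antigen before surgery as the stated denominator.

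The change needs a short amendment to the two sections and no new data. There are two small costs: the displayed denominators fall below 120 per arm, and each visit has two secondary comparisons instead of one composite. Separating the antigens also stops persistent HBsAg from hiding HBeAg loss. It will not give useful power for HBsAg if loss of that antigen is rare.
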